## 1.0 BACKGROUND

---

Persecutory delusions, a fixed belief of deliberate threat, are present in more than 80% of persons during a first episode of psychosis. Persecutory delusions increase risk of suicide, violence, and hospitalization, underscoring the need for effective treatments. Unfortunately, the cognitive and neurobiological mechanisms underlying persecutory delusions are poorly understood and under-investigated, stalling treatment advancement. To address this critical knowledge gap, a randomized-controlled trial (RCT) will be conducted to test whether psychotherapy influences a proposed cognitive mechanism underlying persecutory delusions: abnormal belief updating. Belief updating is the process of integrating new information into existing beliefs systems, and inappropriate belief updating is suggested as a core contributor to delusion severity. Recently, a large-scale clinical trial of 146 psychotic disorder patients with persecutory delusions demonstrated that those who received a brief (6-session), manualized intervention (Worry Intervention Training (WIT)) showed a significantly greater reduction in delusion severity than patients receiving standard care (Freeman et al., *Lancet Psychiatry*, 2015). Despite its efficacy, the cognitive and neurobiological basis of this intervention has not been tested. This proposal will test the hypothesis that abnormal belief updating is a mechanism underlying persecutory delusion severity in psychotic disorder patients that is normalized by WIT psychotherapy. If so, we expect that individuals in the WIT condition will demonstrate significantly greater changes in belief updating over time than individuals receiving Befriending therapy - a supportive psychotherapy that controls for the general factors of therapy, such as weekly engagement and a working alliance. The project will enroll patients with persecutory delusions (N=60) into an RCT of WIT (N=30) or Befriending (N=30) to assess belief updating behaviorally and with fMRI pre/post treatment. The goals of the project are to determine the role of belief updating in persecutory delusion severity and identify neural targets of belief updating changes pre/post treatment, in order to guide future treatment development.

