**In the proposed study, we aim to examine the impact of a previously established psychotherapeutic intervention for persecutory delusions on computational parameters of belief updating (e.g. volatility) and associated brain activation in individuals with psychotic disorders.** Identifying whether belief updating ability changes in response to a therapeutic intervention would advance our understanding of delusions in the following ways: 1) determine whether changes in persecutory delusion severity are associated with changes in belief updating ability, clarifying mechanistic models of delusions; 2) identify neurobiological correlates of changes in persecutory delusion severity, providing future neurobiological targets for intervention; and 3) begin to examine whether psychotherapy is a mechanism-of-change for belief updating ability and persecutory delusions (i.e. whether changes in belief updating parameters mediate the relationship between treatment and change in delusion severity).

We propose an RCT in which individuals randomized to receive either WIT or Befriending therapy, an active control psychotherapy focused on the individual's interests. Inclusion of an active control group will extend previous findings against TAU and begin to address whether cognitive-behavioral interventions (versus the general factors of therapy) impact belief updating. We will recruit approximately 150 participants to enroll 60 adults (18-65 years) with a non-affective psychotic disorder (i.e. schizophrenia-spectrum disorder, delusional disorder). Participants will be randomly assigned to either the WIT (n=30) or Befriending (n=30) groups. The treatment lasts for 8 weeks. Both groups will be asked to complete an fMRI scan at baseline and end of treatment, as well as mid-treatment cognitive and clinical assessments and assessments at 24-week follow-up.

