### **3.0 INCLUSION/EXCLUSION CRITERIA**

---

Inclusion criteria

1. Men and women age 18 - 65.

Protocol Version: 1.5

Date: January 26, 2023

2. Communicative in English.
3. Premorbid IQ >79 (WTAR)
4. Provide voluntary, written informed consent.
5. Physically healthy by medical history.
6. Weight <300 lbs
7. Stable medication regimen over at least the past two weeks, including the use of either an oral or intramuscular administration of an antipsychotic medication.
8. Diagnosis of a non-affective psychotic disorder (schizophrenia, schizoaffective disorder, schizophreniform disorder, delusional disorder, brief psychotic disorder, psychosis NOS) confirmed by Structured Clinical Interview for DSM-5 (SCID), diagnostic interview with a trained clinician, and/or review of electronic medical record.
9. A persecutory delusion scoring at least a 3 on the conviction scale of the Psychotic Symptoms Rating Scale (PSYRATS) that had persisted for at least two weeks and that was not considered the direct result of substance use
10. A clinically significant level of worry, as shown by a score of at least 44 on the Penn State Worry Questionnaire (PSWQ).

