### **8.0 Statistical Considerations**

---

Given that this is a clinical trial, following randomization, all participants who completed the baseline assessment and were randomized will be included in an intent-to-treat analysis, to capture as much data as possible. Regarding the primary aims, **AIM1**: linear regression will be used to test if the severity of persecutory delusions is associated with volatility at baseline, and whether change in delusion severity over 8-weeks is associated with change in volatility across all psychosis participants. These changes are expected to be stronger in the WIT group than in those receiving Befriending. **Aim 2**: Neurobiological underpinnings of volatility will be assessed pre/post treatment in psychotic disorder patients using task-based fMRI. It is hypothesized that activation in the ventral striatum, insula and dlPFC will covary with volatility during a belief updating task. Persecutory delusion severity is expected to be positively associated with volatility-related task activation. Patients receiving WIT are expected to demonstrate normalization (i.e. reduced) activation in these regions post-treatment, which will be associated with delusion severity, representing neurobiological targets for future treatment trials.

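### Aim 1 is stated as 8-week change on change with neither baseline nor arm in the model; run that way, it loses precision between arms and can show co-movement that no individual link produced

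*Protocol*

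**What the plan says.** Protocol Section 8.0 gives Aim 1 two regressions. The first is cross-sectional: "linear regression will be used to test if the severity of persecutory delusions is associated with volatility at baseline". The second relates the two 8-week changes, pooled over arms: "whether change in delusion severity over 8-weeks is associated with change in volatility across all psychosis participants". No covariate is named for either.

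For the arms, Section 8.0 adds only an expectation: "These changes are expected to be stronger in the WIT group than in those receiving Befriending". Section 1.0 states the treatment hypothesis in the same terms, that "individuals in the WIT condition will demonstrate significantly greater changes in belief updating over time than individuals receiving Befriending therapy". No model is given for that comparison.

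The baseline values are available for everyone in the analysis, because "all participants who completed the baseline assessment and were randomized will be included in an intent-to-treat analysis". Section 5.10 repeats the assessments at week 8. The sample is small: "Participants will be randomly assigned to either the WIT (n=30) or Befriending (n=30) groups". Section 2.0 says that finding linked changes would validate belief updating as a treatment target, so the change-on-change test carries much of the trial's conclusion.

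**The concern.** A change score contains the baseline value with its coefficient fixed at -1. Two things follow if the regression is run as it is worded.

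- **Arm contrast.** Fixing the coefficient at -1 rather than estimating it leaves avoidable noise in the outcome. In a trial of 60 that loss matters, and the data that would remove it are already collected.
- **Change-on-change test.** Aim 1 itself expects severity and volatility to be correlated at baseline. If each measure drifts back toward its mean, each change carries part of its own baseline, and the two changes correlate through the baselines alone. Separately, pooling over arms with no arm term means that a treatment that moves both averages produces a correlation across patients, even if within each arm nobody's change in volatility tracks their change in delusions.

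At stake is whether a significant Aim 1 result can be read as belief updating and delusions moving together within patients.

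**Working it through.** **Inputs.** From the protocol: 60 randomised, 30 per arm (30 + 30 = 60, consistent). The protocol gives no power calculation to reproduce, and no alpha, effect size, SD or correlation. Assumed: two-sided 5%, SD 1 at both visits, no dropout. Write rho for the correlation of a measure between baseline and week 8, taken as 0.3 to 0.7, and r for the baseline correlation between severity and volatility, taken as 0.3 to 0.6.

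**Step 1: precision of the arm contrast.** Variance of change = 2(1-rho). Residual variance of the week-8 value given its baseline = 1-rho². The ratio is 2(1-rho)/(1-rho²) = 2/(1+rho), which is never below 1. Power is from the noncentral t distribution with 30 per arm and a 0.5 SD difference. For example, at rho 0.5 the noncentrality is 0.5/(1.000 × √(2/30)) = 1.94 for change and 0.5/(0.866 × √(2/30)) = 2.24 adjusted.

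| rho | variance, change | variance, adjusted | ratio | power, change | power, adjusted |
|---|---|---|---|---|---|
| 0.3 | 1.40 | 0.91 | 1.54 | 36% | 51% |
| 0.5 | 1.00 | 0.75 | 1.33 | 48% | 59% |
| 0.7 | 0.60 | 0.51 | 1.18 | 69% | 76% |

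At rho 0.5, 30 adjusted patients per arm are worth 30 × 1.33 = 40 per arm on unadjusted change. For a 0.6 SD difference at rho 0.5, power is 63% against 75%.

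**Step 2: change on change with no individual link.** Two data models were used, both with no true link between the changes.

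- *Mean reversion:* each week-8 value is rho times its own baseline plus independent noise. The covariance of the changes is r(1-rho)² and each variance is 2(1-rho), so the correlation is r(1-rho)/2. At rho 0.5 and r 0.4 this is 0.4 × 0.5/2 = 0.10.
- *Stable trait plus noise:* correlated stable traits, with independent error at each visit. The traits cancel in the changes, so the correlation is 0.

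If WIT shifts both measures by 0.5 SD and arm is left out, 0.5²/4 = 0.0625 is added to the covariance and to each variance. At rho 0.5 and r 0.4 the correlation becomes (0.10 + 0.0625)/(1 + 0.0625) = 0.153 under mean reversion and 0.0625/1.0625 = 0.059 under trait plus noise.

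Simulated rejection rates at nominal 5%, N = 60, rho 0.5, r 0.4:

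| Model fitted | Mean reversion | Mean reversion + arm shift | Trait plus noise | Trait plus noise + arm shift |
|---|---|---|---|---|
| Change on change, as worded | 12% | 21% to 22% | 5% | 7% to 8% |
| Week-8 severity on change in volatility, baseline severity and arm | 5% | 5% | 5% | 5% |
| Week-8 severity on week-8 volatility, both baselines and arm | 5% | 5% | 24% to 25% | 24% |

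Over rho 0.3 to 0.7 and r 0.3 to 0.6, change on change under mean reversion without an arm shift ranges from 6% to 37%. The model in the second row stayed at 4% to 6% in all settings run.

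**Step 3: why the second row holds.** Under mean reversion, once baseline severity and arm are in the model, what is left of week-8 severity is unrelated to either volatility value. Under trait plus noise, given arm, change in volatility contains only visit error, which is unrelated to severity. The third row fails under trait plus noise because week-8 volatility, given baseline volatility, still carries information about the stable trait, and that trait is correlated with severity.

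**The case against.** The strongest objection is that the omission is read from silence. Section 8.0 does not call the changes raw or unadjusted, covariates are commonly left to a statistical analysis plan, and none is shown here. The quoted regression is a pooled association and not the arm comparison, for which no model is written. A change outcome with its baseline as a covariate gives the same arm estimate as the week-8 outcome adjusted for baseline. All of this stands, so the loss in Step 1 is conditional on how the arms are compared. What remains is that the protocol does fix the method and the form of the outcome for its primary aim, and that this form needs baseline and arm terms the text does not mention.

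A reader might go further and infer that a positive Aim 1 result would merely restate the baseline association. The documents do not support that. The artefact needs both measures to revert to the mean or an arm effect on both; under a stable trait plus noise with no arm effect, the test as worded is valid. The entry cut-offs do not settle which model applies. Section 3.0 requires "A persecutory delusion scoring at least a 3 on the conviction scale" and a minimum worry score, but sets no threshold on volatility, and selection on a cut-off is just as compatible with trait plus noise.

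It is also fair to object that adjusting for everything at baseline is not automatically safer. With both baselines and week-8 volatility in the model, rejection under trait plus noise ran from about 8% to 49% across the settings tried. That objection stands, and it shapes the fix.

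**Conclusion.** The point holds in conditional form. Run as worded, with no baseline or arm term, Aim 1 has two weaknesses. An arm contrast on unadjusted change carries 18% to 54% more variance than the adjusted one, which at a 0.5 SD effect means 7 to 15 points of power. The pooled change-on-change test can exceed its nominal 5%: about 12% under mean reversion and about 21% to 22% with a shared 0.5 SD arm shift, at rho 0.5 and r 0.4. It is correct at about 5% under a stable trait plus noise without arm effects.

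The variance ratio is algebra given equal SDs at the two visits. Every other figure rests on assumed correlations, effect sizes and full follow-up. The protocol does not say which data model applies, so the case for the change is that the recommended mechanism model is valid under both, while the stated one is valid under only one. This is an improvement that should be made, not an error that invalidates the design.

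**What to change.** Amend Section 8.0 as follows.

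1. **Arm contrast:** regress week-8 volatility, and separately week-8 delusion severity, on arm plus the outcome's own baseline value.
2. **Mechanism test:** regress week-8 delusion severity on change in volatility, baseline severity and arm. The coefficient for change in volatility is the same if the outcome is kept as change in severity, so this amounts to adding two covariates to the regression already described. Do not condition on week-8 volatility together with both baselines.
3. **Sensitivity analysis:** report the unadjusted change-on-change result alongside.

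The cost is a wording change, one degree of freedom for the arm contrast and two for the mechanism test. No new data, visits or patients are needed.

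### Neither Aim 1 regression in Section 8.0 estimates the between-arm effect on belief updating that Section 1.0 makes the lead hypothesis, and the arm difference is left as an ambiguous expectation

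*Protocol*

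**What the plan says.** Section 1.0 gives the purpose of the trial: "a randomized-controlled trial (RCT) will be conducted to test whether psychotherapy influences a proposed cognitive mechanism underlying persecutory delusions: abnormal belief updating". It then states a directional hypothesis between the arms: "we expect that individuals in the WIT condition will demonstrate significantly greater changes in belief updating over time than individuals receiving Befriending therapy". Section 2.0 explains that the active control is there to "begin to address whether cognitive-behavioral interventions (versus the general factors of therapy) impact belief updating", and lists among its goals a first look at "whether changes in belief updating parameters mediate the relationship between treatment and change in delusion severity".

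Section 8.0 opens with the analysis population: "all participants who completed the baseline assessment and were randomized will be included in an intent-to-treat analysis". For Aim 1 it names one method with two targets. The first is cross-sectional: "linear regression will be used to test if the severity of persecutory delusions is associated with volatility at baseline". The second concerns change: "whether change in delusion severity over 8-weeks is associated with change in volatility across all psychosis participants". The arms appear in the sentence that follows: "These changes are expected to be stronger in the WIT group than in those receiving Befriending". No model term, contrast or test is attached to that sentence.

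**The concern.** The lead hypothesis is about a difference between randomised groups, and only a comparison by arm estimates it. The first Aim 1 regression uses data from before randomisation. The second relates two post-randomisation changes over everyone. That is an observational association even though it sits inside a randomised trial: it can be strong when WIT does nothing to volatility, and absent when WIT changes volatility a great deal.

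The sentence about the arms does not close the gap, because it supports two readings. It may mean that mean changes are larger under WIT, which is the Section 1.0 hypothesis. It may mean that the association between the two changes is steeper under WIT, which is effect modification. These are different quantities, tested differently and with different power.

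At stake is whether the randomisation and the active control are used for the question they were set up to answer. A significant pooled association could be taken as support for WIT acting on belief updating, which it is not. The mediation question in Section 2.0 also needs an estimate of the effect of treatment on volatility, and Section 8.0 does not name one.

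**Working it through.** **Inputs.** From the protocol: 60 randomised, 30 per arm (Sections 1.0 and 2.0); change measured from baseline to week 8 (Section 8.0). The protocol gives no alpha, power, effect size, SD or dropout, so there is no stated figure to reproduce. Assumed here: two-sided 0.05, normal change scores with unit within-arm SD, the same within-arm correlation r in both arms, and, except in step 3 where stated, no dropout. The standardised shift d is the between-arm difference in mean change divided by the within-arm SD.

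**Step 1: do the two analyses answer the same question?** Simulation of 8,000 trials per scenario. The pooled regression of change in delusion severity on change in volatility is set against a two-sample t-test of change in volatility by arm.

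| d on volatility | d on delusions | within-arm r | pooled association significant | arm comparison significant |
|---|---|---|---|---|
| 0 | 0 | 0.3 | 65% | 5% |
| 0 | 0 | 0.4 | 90% | 5% |
| 0 | 0 | 0.5 | 99% | 5% |
| 0.8 | 0 | 0 | 4.5% | 87% |
| 0.5 | 0.5 | 0 | 7% | 48% |
| 0.8 | 0.8 | 0 | 18% | 87% |

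The first three rows can be checked by hand with Fisher's z, power ≈ Φ(atanh(r)·√57 − 1.96):
- r = 0.3: 0.3095 × 7.550 = 2.337, giving Φ(0.377) = 0.65.
- r = 0.4: 0.4236 × 7.550 = 3.198, giving Φ(1.238) = 0.89.
- r = 0.5: 0.5493 × 7.550 = 4.147, giving Φ(2.187) = 0.99.

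**Step 2: how much association can arm alone create?** If WIT shifts both changes by d through unrelated routes, the pooled correlation is (d²/4)/(1 + d²/4).
- d = 0.5: 0.0625/1.0625 = 0.059.
- d = 0.8: 0.16/1.16 = 0.138.

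These match the last two rows of the table (7% and 18% significant). This route is modest. The larger problem is in the first four rows.

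**Step 3: what could the arm comparison detect?** By the normal approximation, detectable d at 80% power = (1.960 + 0.842) × √(2/30) = 0.72. With the t distribution it is 0.74. With 24 per arm (20% loss, assumed), the normal approximation gives 2.802 × √(2/24) = 0.81. If the baseline-to-week-8 correlation were 0.5 (assumed), baseline adjustment with 30 per arm would give 0.736 × √(1 − 0.25) = 0.64. Unadjusted power is 49% at d = 0.5 and 87% at d = 0.8 (normal approximation).

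**Step 4: what if stronger means a stronger association?** Fisher's z for a difference in correlations, standard error √(2/27) = 0.272.
- 0.5 in WIT against 0.2 in Befriending: (0.549 − 0.203)/0.272 = 1.27, power about 25%.
- 0.5 against 0.0: 0.549/0.272 = 2.02, power about 52%.

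So the choice of reading changes both the question and the chance of an answer.

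**The case against.** The case for the protocol has four parts, and much of it stands.

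First, the pooled regression is not a mistake. Goal 1 in Section 2.0 asks whether changes in delusion severity go with changes in belief updating ability, and this regression answers that directly. It should be kept.

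Second, a reader might infer that Section 8.0 rules out an arm effect, or that the trial would yield no randomised estimate. The text does not support that. Saying that the regression runs over all participants describes the sample, not the covariates. Section 8.0 lists no covariates at all, and its intent-to-treat commitment is compatible with an arm contrast. Model terms are commonly left to a statistical analysis plan, which is not shown.

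Third, a reader might infer that the arm difference would be judged by comparing significance within each arm. Nothing in the protocol proposes this, so it is not part of the point.

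Fourth, the high rates of significance in the working do harm only if the association is presented as a treatment effect, and Section 8.0 calls it an association.

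What this does not remove is the mismatch. Section 8.0 does more than stay silent: under the primary aims it chooses analyses, and these target a different quantity from the hypothesis in Section 1.0. The one sentence that links to that hypothesis has no test and two meanings. A statistical analysis plan that faithfully elaborated Section 8.0 would carry the gap forward.

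**Conclusion.** The point holds as a mismatch between the lead hypothesis and the Aim 1 analyses that the protocol fixes. The pooled change-on-change result is uninformative about a WIT effect on volatility in both directions: about 65% to 99% significant with no such effect (within-arm correlation 0.3 to 0.5), and about 5% significant with an effect of 0.8 SD unrelated to delusions. These figures rest on the assumed alpha, correlations and effect sizes and on full follow-up. The conclusion that the two quantities differ does not depend on the particular values.

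It should be fixed, but it does not show that the trial is unable to answer its question. The data for the arm contrast are already scheduled, the association serves its own goal, and an arm contrast may already stand in a plan that is not at hand.

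**What to change.** In Section 8.0:

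- Add, as the Aim 1 treatment test, an intent-to-treat comparison of week-8 volatility by randomised arm, adjusted for baseline volatility, reported as an estimate with 95% CI. A contrast of change scores would also test the Section 1.0 hypothesis. Baseline adjustment is preferred for precision.
- Keep the change-on-change regression as a separate mechanism analysis, with arm in the model, and describe it as an association.
- State which meaning the sentence about WIT carries: the arm contrast above, or a single arm-by-change-in-volatility interaction.

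The cost is wording only. The reversal learning task is already given at baseline and week 8 (Sections 5.4, 5.6 and 5.10), so no new data are needed. The downside is precision: with 30 per arm, the detectable difference is about 0.74 SD at 80% power, smaller with baseline adjustment and larger with dropout. The interval will be wide and should be reported as such, and a non-significant result should not be read as no effect.
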